### Randomization

Patients participating in the study are randomized after a run-in period, using block randomization at the patient level, at an 1:1 allocation ratio into either one of the two groups: control group or experimental group. Prior to the start of the study the randomization list was generated by a statistician (RT) using a macro [37] in SAS Enterprise Guide 7.13 (SAS Institute Inc., Vary, NC, USA) that automates the random assignment to treatment groups. To prevent predictability of the blocked randomization, block sizes were random and hidden to the researchers and therapists. Since age of the patient can be a confounding variable, in particular being above or below the age of 18 years, age was a stratification factor. Envelopes were numbered in the same order as the randomization list and the group allocation was put in the envelopes after which they were sealed, so that these could be taken to the home of the participant and revealed accordingly.

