### Procedure

Inclusion commenced in September 2018, but inclusion is recently stopped due to Covid-19. Data collection is still ongoing. Participants are being recruited from one academic hospital in the Netherlands where they received their kidney transplant or from the local hospital after referral for post-transplant care. Patients who are eligible for the study are informed about the study by the healthcare professional at the end of their regular appointment. Thereafter the healthcare professional or someone from the research team hands out written information on the study (PIF). The healthcare professional was provided with a standardized script on introducing the study. After having time to consider participation, the researcher contacts the patients by telephone to provide additional information (when needed), answer questions, ask for consent and make an appointment to obtain written consent. This appointment can take place at the patient’s home and the important other is also invited to attend. After written consent from both parties is obtained, the first questionnaires are completed (T0) and the electronic monitoring device is explained and handed out. Since evidence suggests that adherence will be statistically higher when patients start to use the electronic monitoring device [38], a run-in period of 35 days (+/− 7 days) is incorporated. A second appointment is made to coincide with the end of the run-in period (T1), during which a second set of questionnaires is completed by patient and important other, and EM data is collected. Group assignment is revealed after questionnaires have been completed. For the following 6 months patients allocated to the experimental group receive the intervention and the control group receives CAU. Six months after T1 participants are asked to complete questionnaires and EM data is collected (T2). Subsequently, patients continue using the EM device for the follow-up period of 6 months and questionnaires are also completed at the end of this 6 months (T3) (see Fig. 1 for flow-diagram) .

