#### Secondary study parameters

The proportions of adherent participants based on the CAS in both randomization groups will be analyzed with a chi-test with continuity correction. The influence of biological markers on adherence will be analyzed with a logistic regression.

The continuous secondary outcomes will be analyzed with linear multi-level regression analyses. The patients form the upper level, their measures at T1 and T2 the lower level. The covariance structure will be determined with the deviance score applying restricted maximum likelihood. Treatment group, T2, the group-T2 interaction and age will be postulated as fixed effects. In case of an abnormal distribution of the scores, an appropriate transformation (logarithmic, polynomial or Blom [73]) will be applied. If no satisfying transformation can be found, the outcome will be dichotomized on the median, and a multilevel logistic regression analysis will be performed. Binary outcomes will be analyzed with multilevel logistic regression analysis, using the same levels and fixed effects as described for linear multi-level regression analysis.

To analyze whether the intervention is sustainable 6 months after the treatment, a logistic multilevel analysis will be applied including the T1, T2 and T3 measures. Adherence will be the dependent variable, and treatment group, T2, T3 and group-time interactions will be the fixed effects. The group-T2 interaction effect will present the differential intervention effect, and the T2-T3-group contrast is the effect of interest for sustainability.

To answer the question when the intervention influences the adherence most, a multi-level logistic regression analysis will be applied. The EM devices can be read every 30 days, resulting in a baseline and 6 repeated measures (at 65, 95, 125, 155, 185 and 215 days). The fixed part of the model will include treatment group, the six follow-up time points and interactions.

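### Continuous secondary outcomes: a free group effect at the pre-randomisation T1, and a last-resort median split, give away precision that a change of wording would keep

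*Protocol article*

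**What the plan says.** The protocol article, under Secondary study parameters, prescribes a linear multilevel model for the continuous secondary outcomes. On the data it says "The patients form the upper level, their measures at T1 and T2 the lower level", and on the model "Treatment group, T2, the group-T2 interaction and age will be postulated as fixed effects". It does not name the treatment-effect coefficient for these outcomes. For the sustainability model, which has the same structure with T3 added, it says "The group-T2 interaction effect will present the differential intervention effect".

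T1 comes before allocation. The Randomization section says "Patients participating in the study are randomized after a run-in period", and the Procedure section says of the T1 visit "Group assignment is revealed after questionnaires have been completed".

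For distributional problems there are two steps. The first is "In case of an abnormal distribution of the scores, an appropriate transformation (logarithmic, polynomial or Blom [73]) will be applied". Only after that comes "If no satisfying transformation can be found, the outcome will be dichotomized on the median, and a multilevel logistic regression analysis will be performed". The text does not define a satisfactory transformation, nor say whether the median is taken at T1, at T2 or over both.

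**The concern.** Two separate choices lose information that the trial already collects.

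**Baseline.** Because T1 precedes allocation, the arms have the same expected T1 mean by design. A treatment-group main effect lets the model estimate a T1 difference that is known to be zero in expectation. Chance imbalance at T1 is then subtracted in full from the T2 difference, rather than in proportion to how well T1 predicts T2.

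**Median split.** Once reached, the fallback reduces a graded score to high or low at a cut that depends on the sample and has no clinical meaning. The reported effect also changes from a mean difference to an odds ratio around that cut.

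Self-management, self-efficacy, mental health and social support are stated objectives (Table 1) and rest largely on this model. The sample size was set for the binary primary outcome only, so there is no planned reserve of power for them.

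**Working it through.** **Inputs.** The plan gives no power or precision figure for the continuous secondary outcomes, so there is none to reproduce. From Power calculation: 81 per arm and 10% drop-out, so 81 × 0.90 = 72.9, about 73 evaluable per arm. From Randomization: allocation "at an 1:1 allocation ratio". The T1-T2 correlation rho and the true effects are not in the protocol and are assumed over a range. Tests are two-sided at 0.05, also an assumption.

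**1. Free group effect against common T1 mean.** Take n per arm, SD sigma at both visits and complete data.

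- As written, group-by-T2 is the difference in mean change: variance 4·sigma²·(1 − rho)/n.
- With a common T1 mean, or T1 as a covariate: variance 2·sigma²·(1 − rho²)/n in large samples.
- Ratio: 4(1 − rho) / [2(1 − rho)(1 + rho)] = 2/(1 + rho).

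| rho | 4(1 − rho) | 2(1 − rho²) | Ratio |
|---|---|---|---|
| 0.3 | 2.80 | 1.82 | 1.54 |
| 0.5 | 2.00 | 1.50 | 1.33 |
| 0.7 | 1.20 | 1.02 | 1.18 |
| 0.9 | 0.40 | 0.38 | 1.05 |

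Comparing T2 alone has variance 2·sigma²/n. Below rho = 0.5 the model as written is therefore less precise than ignoring T1 altogether.

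Simulated power (4,000 trials, normal scores, 73 per arm):

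| True T2 difference | rho | Common T1 mean | As written |
|---|---|---|---|
| 0.5 SD | 0.3 | 87% | 72% |
| 0.5 SD | 0.5 | 94% | 86% |
| 0.5 SD | 0.7 | 99% | 97% |
| 0.4 SD | 0.3 | 71% | 53% |
| 0.4 SD | 0.5 | 79% | 67% |
| 0.4 SD | 0.7 | 92% | 88% |

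Under no effect, rejection rates were 4.5% to 5.4% for these two analyses and for a median split of the same normal scores.

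**2. Median split where it would be reached.** Blom is a rank-based normal-score transformation, so a score with few ties becomes close to normal. What remains is mainly scores with many patients tied at a floor or ceiling. Such scores were simulated as a latent normal variable with a floor, a 0.47 SD shift (which gives about 80% t-test power without a floor), 73 per arm and one time point.

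| Score | Share at floor | Rank test | Median split | Loss (points) |
|---|---|---|---|---|
| Integer, 6,000 trials | 20% | 0.77 | 0.63 | 14 |
| Integer | 30% | 0.75 | 0.62 | 13 |
| Integer | 40% | 0.73 | 0.62 | 11 |
| Latent normal with floor, 4,000 trials | 30% | 0.78 | 0.61 | 17 |
| Same | 50% | 0.73 | 0.60 | 13 |
| Same | 60% | 0.70 | 0.61 | 9 |
| Same | 70% | 0.67 | 0.62 | 5 |

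In the integer series a plain t-test on the raw scores had power 0.77, 0.75 and 0.72, close to the rank test.

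**The case against.** The strongest defence is that nothing here is invalid. A model with group, time and their interaction is standard and unbiased under randomisation, and its advantage or disadvantage depends on a correlation the protocol does not give; at 0.9 the variance penalty is only 5%. The median split is a last resort behind three transformations, and one of them, Blom, already supplies a rank-based analysis for most skewed scores. Only secondary outcomes are involved, and the protocol claims no power for them. All of this stands, and it limits the point to precision.

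It does not remove the point. Both rules are fixed in the text rather than left open, both alternatives use data already collected, and each is at least as precise under the assumptions shown.

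A reader might infer more than the protocol supports:

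- *That every non-normal score is split at the median.* It is not; transformation comes first. Normal scores, and skewed scores that a log or Blom transformation repairs, never reach the split, so power losses computed on such data do not describe this plan.
- *That particular outcomes are bound for the split.* The protocol reports no score distributions. Intra-patient variability, calculated from repeated tacrolimus concentrations, should have few ties and would ordinarily be handled by transformation.
- *That the plan misunderstands the normality assumption because it speaks of scores rather than residuals.* In a condensed article this is too little to go on.

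**Conclusion.** The point holds as a precision improvement for the continuous secondary outcomes.

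The free T1 group effect inflates the variance of the treatment contrast by 2/(1 + rho), that is by 54%, 33%, 18% and 5% at rho 0.3, 0.5, 0.7 and 0.9. This rests on complete data, equal variances at T1 and T2, and an assumed rho; at high correlation the loss is negligible.

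Where the median split is reached, it costs about 5 to 17 percentage points of power against a rank test, shrinking as the share at the floor grows. This rests on an assumed latent normal score, a 0.47 SD shift and single-time-point tests, which stand in for the two-visit multilevel logistic model actually planned. How often the fallback would be used cannot be judged from the protocol.

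A reader might take this for a bias or a false-positive problem. It is neither: simulated type I error stayed near 5%, and the chi-square analysis of the primary outcome is untouched.

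**What to change.** 1. **Baseline.** Remove the treatment-group main effect from the linear multilevel model, keeping T2, group-by-T2 and age, so that the arms share one T1 mean. This stays within the planned framework. Alternatively, analyse T2 with T1 as a covariate. State that group-by-T2 (or the adjusted group difference) is the treatment effect for these outcomes.
2. **Fallback.** Delete the median split. Where no transformation is adequate, use a proportional-odds mixed model, or robust or bootstrap intervals for the mean difference on the original scale. The raw-score comparison was checked only up to 40% at the floor, so the ordinal model is the better-supported choice for heavier floors.

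The cost is wording: no new data, visits or patients. The one small drawback is that proportional-odds results are less familiar to clinical readers. Both changes should be fixed before outcome data are compared by arm.

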### Aim and objectives

The aim of the present study is to test the effectiveness of the MARS-intervention in promoting immunosuppressive medication adherence and self-management among adolescent and adult kidney transplant recipients compared to care-as-usual (CAU).

We translated this aim into a primary research objective and several secondary objectives (Table 1).

**Table 1 Tab1:** Overview of objectives and measures at different time-points

Objectives	Measures	T0	T1	T2	T3

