	**Medical data patient file**				
	Intra patient variability (IPV)	X	X	X	X
	Rejection of the graft (treatment for rejection)			X	X
	Graft loss			X	X
	Kidney functioning (eGFR)	X	X	X	X

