### Study population

#### Patients

The study population consists of kidney transplant recipients, aged 12 years and older, with no limitation to time since transplantation. Patients are required to have a subscription of IM and have a functioning graft at the time of inclusion. Graft functioning may be deteriorating, but as long as IM is required and the patient is not expected to be on dialysis within the next 3 months they can be included. In order to avoid convenience sampling multiple ways of assessing eligibility are being used. Kidney transplant recipients are eligible for inclusion when non-adherence is signaled by either themselves (self-report), or by the nephrologist or nurse practitioner (collateral report – professional) or someone in the patient’s social network (collateral report- social network). These three indicators combined form a composite adherence score (CAS). An affirmative answer on one (or more) of these indicators is sufficient to invite the recipient to participate. A CAS is more sensitive than using a single measure of non-adherence [31, 34–36]. Furthermore, non-adherent patients who do not explicitly acknowledge their non-adherence as a problem can be identified using the CAS. Professionals form an impression of adherence through, for example, conversations with the patient, clinic attendance and blood assay monitoring. Potential participants who meet any of the following criteria will be excluded from participation: 1) patients classified as adherent on all three of the indicators forming the CAS, 2) patients on dialysis or who are expected to start dialysis within the next 3 months, 3) patients who do not understand the Dutch language, 4) patients prior to their first transplant, and 5) patients with severe psychopathology or ongoing psychological treatment. In contrast with most other studies, patients with cognitive limitations (incapacitated) are not excluded from participation because their representative(s) and social network can be involved in the intervention and give complementary information regarding problems the patient is facing.

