#### Secondary outcome measures patient

##### Medication adherence

In addition to EM, other secondary outcome measures are also used to assess medication adherence. This is in line with the suggestion of Schafer-Keller et al. [31] to combine several measurements to reach maximum validity. We calculate the Composite Adherence Score (CAS) combining the following measures:
Patient self-report about non-adherence (Basel Assessment of Adherence to Immunosuppressive Medications Scale; BAASIS©-interview).Collateral report – important other about patients’ non-adherence using an Adjusted Basel Assessment of Adherence to Immunosuppressive Medications Scale; BAASIS©-interview.Collateral report – professional about patients’ non-adherence based on varying medication blood levels or behavioral indicators such as missed appointments.

The BAASIS takes both taking and timing into account, as well as drug holidays, reduction of medication doses, and persistence over the last 4 weeks. An affirmative answer on missing a dose (taking), taking IM ≥ 2 h before or after prescribed dosing time (timing), reducing the IM dose, or stopping taking medication completely (persistence) leads to being categorized as non-adherent. Patients also rate their own adherence using a visual analogue scale ranging from 0% (never take medication as prescribed) to 100% (always take medication as prescribed). The BAASIS is recommended for the use as a self-report measure among transplant recipients [1, 48]. An adjusted version of the BAASIS is used for the collateral report of the important other regarding the medication adherence of the patient. The important other is presented with the same questions as the patients on the IM adherence of the patient. Additional to the yes/no, the important other is allowed to answer I don’t know.

The collateral report from the professional is based on a yes/no answer as to whether they think a patient is adherent.

Furthermore, medical data derived from the medical records is also used to give an impression of adherence. We calculate intra patient variability (IPV) using whole blood concentrations of tacrolimus in multiple measurements over time within patients. The method previously described by Borra et al. [49] is used to make this calculation. The following transplant outcomes are collected: rejection of the graft (yes/no), graft loss (yes/no) and kidney functioning (eGFR).

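### The T1/T2 multilevel logistic model prescribed for binary outcomes cannot estimate its treatment-effect term for graft rejection and graft loss, which Table 1 schedules only at T2 and T3

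*Protocol article*

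**What the plan says.** All references are to the protocol article.

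- **Outcome type.** The Medication adherence part of the patient secondary outcomes lists the transplant outcomes as "rejection of the graft (yes/no), graft loss (yes/no) and kidney functioning (eGFR". Rejection and graft loss are therefore binary.
- **Schedule.** Table 1 ("Overview of objectives and measures at different time-points") has columns T0 to T3. The rows for "Rejection of the graft (treatment for rejection" and for graft loss are marked at T2 and T3 only. In the same block, intra-patient variability and eGFR are marked at all four visits.
- **Model.** Under Secondary study parameters the linear model is set up as follows: "The patients form the upper level, their measures at T1 and T2 the lower level". Then: "Treatment group, T2, the group-T2 interaction and age will be postulated as fixed effects". For binary outcomes: "Binary outcomes will be analyzed with multilevel logistic regression analysis, using the same levels and fixed effects". Among the secondary outcomes only the composite adherence score has its own between-group test. No exception is made for outcomes without a T1 measure.
- **T3.** For sustainability, "a logistic multilevel analysis will be applied including the T1, T2 and T3 measures", with adherence named as the dependent variable.
- **Eligibility.** Patients must "have a functioning graft at the time of inclusion", and those expected to need dialysis within three months are excluded.

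**The concern.** The binary-outcome rule presupposes a T1 value, because its treatment effect is the group-T2 interaction: the between-arm difference at T2 relative to that at T1. Rejection and graft loss have no T1 value in the schedule. The rule therefore sends two outcomes to a model that their data cannot support.

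At stake is whether the comparison of these outcomes is fixed in advance. An analyst who follows the text will meet a model that is not identified and must improvise: drop terms, fill in T1, or switch method. Each choice gives a different analysis, made after the data are in. The Discussion counts the assessment of transplant outcomes among the study's strengths, so their analysis should be one that can be run.

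**Working it through.** The plan gives no figure to reproduce here. The check sets the model against the schedule.

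**Inputs.** Fixed effects and levels come from Secondary study parameters, measurement times from Table 1, and 81 patients per arm (162 in total) from the Power calculation. Age was simulated, and only to fill its column.

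**1. The model.** For patient i at time t:

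logit p = b0 + b1·group + b2·T2 + b3·group×T2 + b4·age + u_i

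- At T1: b0 + b1·group + b4·age + u_i
- At T2: (b0 + b2) + (b1 + b3)·group + b4·age + u_i

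With T2 rows only, the data inform b0 + b2, b1 + b3 and b4. They cannot separate b2 from b0, or b3 from b1.

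**2. Rank of the fixed-effects design matrix (5 columns).**

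| Rows available | Rank |
|---|---|
| T1 and T2 | 5 of 5 |
| T2 only (rejection, graft loss) | 3 of 5 |

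The rule works for outcomes measured at T1 and fails for these two. One binary row per patient also leaves no within-patient replication from which to estimate the variance of u_i.

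**3. Filling T1 with no event.** This was tried with assumed T2 counts of 8/81 versus 4/81 and all T1 values zero (fixed effects only, age omitted, Newton steps):

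| Iteration | T2 coefficient | SE of group×T2 |
|---|---|---|
| 5 | 3.99 | 3.6 |
| 10 | 8.99 | 42.6 |
| 15 | 13.99 | 518.4 |
| 20 | 18.99 | 6,315.7 |
| 25 | 23.99 | 76,941.2 |

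This is quasi-complete separation. The T1 log-odds run to minus infinity in both arms, so their difference, b1, is undetermined. Since b3 is the T2 difference minus b1, it is undetermined too. The fitted b3 stays at -0.75 only because the arms are equal in size and the iterations start at zero, which holds b1 at 0. The event counts are invented, but the divergence follows from the all-zero T1 rows whatever the T2 counts.

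For graft loss the all-zero T1 is close to structural, given the eligibility rules and a run-in of 35 days. For rejection it is not: a functioning graft does not exclude earlier treated rejection.

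**4. What is still estimable.** In the same example the T2 contrast b1 + b3 is an ordinary log odds ratio:

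- ln[(4/77)/(8/73)] = ln(292/616) = -0.746
- SE = √(1/4 + 1/77 + 1/8 + 1/73) = √0.4017 = 0.634

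This is finite and stable, but it comes from a one-row-per-patient comparison and not from the stated model.

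**5. The sustainability model.** Its six columns are intercept, group, T2, T3, group×T2 and group×T3. Without T1 rows the rank is 4 of 6, because T2 + T3 equals the intercept and the two interactions add up to group. The group-T2 effect is again not estimable; only the change in the group difference between T2 and T3 would be. The model is in any case stated for adherence.

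**The case against.** The strongest reply is that little is lost. Drop the two aliased terms and the random intercept, and a plain logistic comparison at T2 remains, as step 4 shows. A competent analyst would do this, the outcomes are two among many secondary measures, and the primary test does not depend on them. All of that is correct, and it limits the size of the point. It does not remove the point: the reduced model is not the one the article prescribes, and the article gives no rule for reaching it.

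Three stronger readings are tempting, and the documents do not support them.

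- A reader might infer that the treatment effect is undefined or infinite and that no valid comparison of the arms exists. Only the interaction term is unidentified; the T2 odds ratio can be recovered from the same data.
- A reader might infer that both outcomes are necessarily zero at T1. That follows for graft loss only. Time since transplantation is unrestricted and deteriorating grafts are admitted, so treated rejection before T1 is possible.
- A reader might infer that the T3 events are never analysed or are discarded. The article merely states no such analysis, and as a condensed account it may leave this to a fuller document. The continuous secondary outcomes are likewise modelled on T1 and T2 only.

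**Conclusion.** The point holds as a contradiction between Table 1 and the binary-outcome rule. For graft rejection and graft loss the stated model has one row per patient, its group-T2 term is aliased with group, and its random intercept is not identifiable. This rests on the printed schedule alone and on no assumption about event rates. Entering no event at T1 fails for graft loss, on the near-certain premise that almost no graft is lost before T1.

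The effect is limited: two secondary outcomes have a prescribed analysis that cannot be run as written. The sample size, the primary comparison and the outcomes measured at T1 are untouched.

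**What to change.** Exempt graft rejection and graft loss from the T1/T2 multilevel rule and give them their own sentence. For example:

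*Graft rejection and graft loss, which have no T1 measure, will be compared between the randomised groups as the cumulative proportion of patients with an event from randomisation to T2 and from randomisation to T3, with one record per patient, and reported as an effect estimate with 95% confidence interval.*

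Name one method in advance. Fisher's exact test with a risk difference and interval would do, as would ordinary or Firth logistic regression with group and age, which keeps the age term of the current rule. Firth's version is the safer logistic choice if events prove sparse; the documents give no event rate, so that is a precaution. Including T3 uses data that Table 1 already schedules.

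The cost is a change of wording, with no new visit, measurement or patient. The article reports data collection as still ongoing, so the sentence should be fixed before any comparison of these outcomes by arm.

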	**Collateral report Health Care Professional**				
	Adherent to medication (Y/N)	X	X	X	X
To test the effectiveness of the MARS-intervention (experimental group) in promoting self-management in comparison to CAU (control group).	**Questionnaires patient**				
	Self-management skills (PiH-NL)	X	X	X	X

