### Statistical analysis

#### Power calculation

To our knowledge there was no (multi) systemic intervention study carried out among kidney transplant recipients at the time this project commenced, making it difficult to conduct a power analysis based on a comparable study. Therefore, the power calculation is based upon a behavioral intervention study among a group of heart, liver and lung transplanted patients [72]. The intervention group showed an adherence proportion of 95.1% and the control group a proportion of 79.1%. As the MARS-intervention is more intensive than the intervention of Dobbels et al. [72] we will perform an interim analysis when half of the participants have been included. We applied a 2-sided alpha of 0.029 and a power of 0.80. Anticipating a drop-out of 10%, this led to a target of 81 participants in both groups, a total of 162.

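### For the separate binary adherence indicators, the planned group-T2 interaction carries chance T1 differences into the treatment effect and loses power; a T2 comparison adjusted for T1 avoids this

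*Protocol article*

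**What the plan says.** Under Secondary study parameters, the continuous outcomes get a two-level model: T1 and T2 measures within patients, with group, T2, their interaction and age as fixed effects. For binary outcomes the article adds: "Binary outcomes will be analyzed with multilevel logistic regression analysis, using the same levels and fixed effects". The following paragraph, on sustainability, names the group-T2 interaction as the differential intervention effect.

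Table 1 lists patient BAASIS, the important other's BAASIS and the professional's judgement ("Adherent to medication (Y/N") as separate adherence measures at T0, T1, T2 and T3. The section on secondary outcome measures also combines them into the Composite Adherence Score (CAS). The CAS is not put through the interaction model; it is compared between groups with a continuity-corrected chi-square test.

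The same three sources decide entry. Under Patients: "Kidney transplant recipients are eligible for inclusion when non-adherence is signaled by either themselves (self-report), or by the nephrologist or nurse practitioner", or by someone in the social network. One signal suffices: "An affirmative answer on one (or more) of these indicators is sufficient to invite the recipient to participate". Only patients adherent on all three are excluded.

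Randomisation is "at an 1:1 allocation ratio" and takes place after the run-in. Under Procedure, the allocation is revealed once the T1 questionnaires are complete.

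**The concern.** T1 precedes allocation, so the true group difference at T1 is zero. The planned model estimates that difference anyway and subtracts it from the T2 difference. On the log-odds scale each arm's T1 cell adds roughly 1/(n × p0 × (1 − p0)) to the variance of the interaction, where p0 is the share adherent at T1. The term is never zero, and it grows quickly as p0 falls.

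The entry rule makes a low p0 possible. Patients are recruited because at least one of these indicators showed non-adherence, and BAASIS is strict: one missed, mistimed or reduced dose in four weeks counts.

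The Discussion relies on these measures to triangulate the electronic monitoring (EM) result. If the analysis of the separate indicators is needlessly weak, a non-significant result on them could be read as disagreement with EM when it reflects only the choice of model.

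**Working it through.** **Inputs.** From Power calculation: "We applied a 2-sided alpha of 0.029 and a power of 0.80"; planning rates 95.1% and 79.1%; "Anticipating a drop-out of 10%, this led to a target of 81 participants in both groups, a total of 162". Assumed: two-sided 0.05 for secondary outcomes; T2 rates of 30% vs 55%, or the planning rates borrowed from EM; the range of p0; random-intercept SD 1.5 in the simulations.

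**1. The plan's own sample size.** Arcsine effect size h = 2(asin√0.951 − asin√0.791) = 0.503. Then n = 2 × ((2.183 + 0.842)/0.503)² = 72.3 per arm. Dividing by 0.9 gives 80.3, so 81 per arm and 162 in total. The stated figure is reproduced. Evaluable per arm: 81 × 0.9 = 72.9, about 73.

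**2. Hand formula, with T1 and T2 treated as uncorrelated.** Var(interaction) = 2/(n p0(1 − p0)) + 1/(n pC(1 − pC)) + 1/(n pT(1 − pT)), where pC and pT are the T2 rates. Example with 30% vs 55% and p0 = 10%:
- T1 part: 2/(73 × 0.09) = 0.304.
- T2 part: 1/(73 × 0.21) + 1/(73 × 0.2475) = 0.121.
- SE = √0.425 = 0.652; log odds ratio = 1.05; z = 1.61; power about 36%.
- T2 alone: SE = √0.121 = 0.347; z = 3.02; power about 85%.

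| p0 | 30% vs 55% | 79.1% vs 95.1% |
|---|---|---|
| 2% | 13% | 23% |
| 5% | 24% | 39% |
| 10% | 36% | 51% |
| 20% | 49% | 60% |
| 30% | 55% | 63% |
| 50% | 59% | 65% |
| T2 only | 85% | 76% |

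**3. Simulation of the random-intercept model.** This lets T1 and T2 correlate, which favours the interaction. Settings: 73 per arm, likelihood-ratio tests, 300 runs per setting, age omitted.

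| p0 | Interaction, 30% vs 55% | Interaction, 79.1% vs 95.1% |
|---|---|---|
| 2% | 0.22 | 0.29 |
| 5% | 0.32 | 0.37 |
| 10% | 0.46 | 0.54 |
| 20% | 0.65 | 0.64 |
| 30% | 0.71 | 0.73 |
| 50% | 0.78 | 0.77 |
| T2 chi-square, all p0 | 0.81–0.85 | 0.79–0.85 |
| Group means equal at T1, all p0 | 0.85–0.91 | 0.86–0.90 |

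A separate simulation at SD 1.5 compared the interaction with a logistic regression of T2 status on group adjusted for T1 status: 0.32–0.79 against 0.82–0.93 over the T1 shares tried. At shares of 30 to 50% the interaction had about 0.66–0.79. With SD 3 the adjusted regression was again the more powerful at every share tried.

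**4. Empty T1 cell in at least one arm.** 1 − (1 − (1 − p0)^73)² gives 41% at p0 = 2%, 5% at 5% and 0.1% at 10%.

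**5. What the entry rule implies for p0.** If every patient failed exactly one of the three indicators, the average adherent share per indicator at entry would be 2/3 = 67%. Only the composite is 0% adherent at entry by construction.

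**The case against.** A reader might infer that, because these indicators admit patients, hardly anyone is adherent on them at T1, so that the interaction loses most of its power or cannot be estimated. The article does not support that.

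- One signal of three is enough, so no single indicator is driven to zero, and no T1 share is stated for any of them.
- BAASIS looks back four weeks, so at T1 it describes the 35-day run-in. The Procedure section expects higher adherence when monitoring starts. Regression to the mean works in the same direction.
- The one measure that selection does empty, the CAS, is tested by chi-square. The combined cross-check on EM is therefore intact.
- Very low power figures near an empty cell depend on the test. At p0 = 2% with 30% vs 55%, one simulation gave 6% by Wald and 23% by likelihood ratio. The article prescribes neither.
- The article does not name the three indicators as outcomes of the interaction model. That follows from their separate listing in Table 1 and the general sentence on binary outcomes.
- These are secondary outcomes for which no power is claimed.

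All of this stands, and it limits the size of the point. It does not remove it. The model is specified, so this is not a detail left to an analysis plan. The cost of a free T1 group effect also does not depend on a near-empty cell: the interaction had less power than every alternative simulated, at every T1 share tried.

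**Conclusion.** The point holds as a loss of efficiency in a specified model for the separate binary adherence indicators. The loss is modest if 30 to 50% are adherent at T1: power about 0.66–0.79 against 0.82–0.93. It reaches about half or more at 5% or less; at 5% the interaction has 0.32 and 0.37, against 0.81 and 0.79 for an unadjusted T2 chi-square. Failure to estimate the effect is a real risk only in that low range. Where the trial falls is unknown, because the T1 shares are not given.

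The figures rest on 73 evaluable per arm, two-sided 0.05, the assumed T2 rates and a random-intercept SD of 1.5. The direction rests only on randomisation following T1. The primary EM analysis and the CAS comparison are not affected.

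**What to change.** For patient BAASIS, the important other's BAASIS and the professional's yes/no, replace the T1/T2 interaction model with a logistic regression of T2 status on randomised group, with T1 status and the age stratum as covariates. Do the same for T3. Alternatively, keep the two-row model but constrain the group means to be equal at T1, which serves the same purpose with similar power. Either choice fits the between-group comparison already planned for the CAS.

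The cost is a change of wording; T1 status is already collected. The downside is interpretive: the adjusted odds ratio is conditional on T1 status and, because odds ratios are non-collapsible, is not numerically the same as the patient-specific interaction odds ratio. The report should say which one is given.
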